# Grouping Factors

None

# Registration Procedures

- 1. Pre-Registration

**Call the Registration Office [contact]) prior to discussing protocol entry with the patient to ensure that a place on the protocol is open to the patient.**

The lag between pre-registration and registration should be no more than 28 days.

- 1. Pre-registration

To pre-register a patient, [contact]) a completed eligibility checklist to the Mayo Clinic Cancer Center (MCCC) Registration Office between 8 a.m. and 4:30 p.m. central time Monday through Friday.

- 1. IRB approval(s) is required for each treating site.

In addition to submitting initial IRB approval documents, ongoing IRB approval documentation must be on file (no less than annually). If the necessary documentation is not submitted in advance of attempting patient registration, the registration will not be accepted and the patient may not be enrolled in the protocol until the situation is resolved.

When the study has been permanently closed to patient enrollment, submission of annual IRB approvals is no longer necessary.

- 1. Verifications

Prior to accepting the pre-registration, the registration/randomization application will verify the following:

- - - IRB approval at the registering institution
    - Patient pre-registration eligibility
    - Existence of a signed consent form
    - Existence of a signed authorization for use and disclosure of protected health information
  1. Pre-registration tests/procedures

Pre-registration tests/procedures (see Section 4.0) must be completed within the guidelines specified on the test schedule.

- 1. Correlative Research

A mandatory correlative research component (tissue and blood) is part of this study; the patient will be automatically pre-registered onto this component (see Sections 3.17 and 14.2).

An optional correlative research component (tissue) is part of this study; there will be an option to select if the patient is to be pre-registered onto this component (see Section 17.32).

- - - Patient has/has not given permission to give his/her tissue sample for research testing.
  1. Other permissions

At the time of pre-registration, the following will be recorded:

- - - Patient has/has not given permission to store and use his/her sample(s) for future research of melanoma at Mayo.
    - Patient has/has not given permission to store and use his/her sample(s) for future research to learn, prevent, or treat other health problems.
    - Patient has/has not given permission for MCCC to give his/her sample(s) to researchers at other institutions.
  1. Registration Procedures

**Prior to discussing protocol entry with the patient, call the MCCC Registration Office [contact]) for dose level and to insure that a place on the protocol is open to the patient.**

- 1. To register a patient, [contact]) a completed eligibility checklist to the Mayo Clinic Cancer Center (MCCC) Registration Office between 8 a.m. and 4:30 p.m. central time Monday through Friday.
  2. Documentation of IRB approval must be on file in the Registration Office before an investigator may register any patients.

In addition to submitting initial IRB approval documents, ongoing IRB approval documentation must be on file (no less than annually) at the Registration Office ([contact]). If the necessary documentation is not submitted in advance of attempting patient registration, the registration will not be accepted and the patient may not be enrolled in the protocol until the situation is resolved.

When the study has been permanently closed to patient enrollment, submission of annual IRB approvals to the Registration Office is no longer necessary.

- 1. Prior to accepting the registration, the registration/randomization application will verify the following:
     - IRB approval at the registering institution
     - Patient eligibility
     - Existence of a signed consent form
     - Existence of a signed authorization for use and disclosure of protected health information
  2. Treatment on this protocol must commence at Mayo Clinic Rochester under the supervision of a medical oncologist.
  3. Treatment cannot begin prior to registration.
  4. Pretreatment tests/procedures (see Section 4.0) must be completed within the guidelines specified on the test schedule.
  5. All required baseline symptoms (see Section 10.6) must be documented and graded.
  6. Study drug is available on site.

# Protocol Treatment

- 1. Treatment Schedule

Use actual weight or estimated dry weight if fluid retention Cycle 1 treatment = 28 days

All subsequent treatment cycles = 21 days (±3 days)

| Drug | Dose | Treatment | Retreatment |
| --- | --- | --- | --- |
| Ibrutinib | assigned at registration | PO daily (Day 1 to 28  of Cycle 1, then Day 1- 21* on subsequent cycles) | Every 21 days  (±3 days)  until confirmed progression |
| Pembrolizumab | 200 mg | IV injection on Day 8 of Cycle 1 and then Day 1 of each  subsequent cycle | Every 21 days (±3 days) until confirmed progression |

* Patients should receive a sufficient quantity of ibrutinib to last until the next scheduled treatment visit.

- 1. Determination of Maximum Tolerated Dose (MTD)
  2. Dose Escalation Scheme

| Dose level | Ibrutinib** |
| --- | --- |
| -1 | 140 mg |
| 0* | 280 mg |
| 1 | 420 mg |

* Starting dose level

** If the patient has clinical or laboratory evidence of liver failure during the treatment, then calculate the Child-Pugh score and adjust the ibrutinib dose (see Table 8.3).

NOTE: Doses will not be escalated in any individual patient.

- 1. MTD Determined

As of MCCC Amendment 6, the MTD has been determined to be Dose Level 1. Dose Level 1 will be used for the expansion cohort.

- 1. Dose Limiting Toxicities

Dose limiting toxicities (DLT) are defined to be:

| ***Toxicity*** | ***DLT Definition*** |
| --- | --- |
| Hematologic | Grade 4 ANC, Grade 4 Hgb, or PLT <25,000 |
| Renal | Serum creatinine ≥2 times baseline |
| Neurologic | ≥Grade 2 neurosensory or neuromotor toxicity |
| Other nonhematologic | ≥Grade 3 per NCI Common Terminology Criteria for Adverse Events (CTCAE) version 4.0* |

*Grade 3 rash or fever despite maximal supportive treatment(s) will be considered dose-limiting; all grade 4 rash and fever will be considered a DLT.

The maximum tolerated dose is defined as the highest dose level among those tested where at most one out of 6 patients develops a DLT prior to the start of their second cycle of treatment and the next highest dose level is such that 2 out of a maximum of 6 patients treated at this dose level developed a DLT prior to the start of their second cycle of treatment.

- 1. Dose escalation plan

NOTE: As of MCCC Amendment 6, the MTD has been determined to be Dose Level 1. A minimum of 2 or a maximum of 6 patients will be accrued to a given dose level.

For all dose levels, patients will be accrued so that at any given time no more than 2 patients will be receiving their first cycle of treatment **and** acute adverse event data over the first treatment cycle for all other patients treated at the current dose level is known.

If, at any time in the enrollment process, 2 patients treated at the current dose level develop a DLT during the first cycle of treatment, enrollment will be closed to that dose level. Enrollment will be re-opened to the next lower dose level if fewer than 6 patients have been treated at that dose level.

If none of the first 3 patients treated at a given dose level develops a DLT during the first cycle of treatment, enrollment to the dose level will be closed and enrollment will reopen at next higher dose level. If there are no other higher dose levels to be tested, three additional patients will enrolled at the current dose level to confirm MTD.

If one of the first 3 patients treated at a given dose level develops a DLT during the first cycle of treatment, three additional patients will enrolled (sequentially) on that dose level.

If, at any time in the enrollment of these 3 additional patients, a patient develops a DLT, enrollment will be closed to that dose level. Enrollment will be re-opened to the next lower dose level if fewer than 6 patients have been treated at that dose level.

If none of these 3 additional patients develops a DLT during the first cycle of treatment, enrollment to that dose level will be closed and enrollment will reopen at next higher dose level. If there are no other higher dose levels to be tested, this will be considered the MTD.

- 1. Replacement

If a patient fails to complete the first cycle of treatment for reasons other than toxicity, an additional patient will be enrolled to replace this patient. For these instances, a specific notation will be made for review by the Scientific Progress Review Committee.

- 1. Return to consenting institution

The patient must return to the consenting institution for evaluation and treatment at least every 21 days (± 3 days) during treatment.

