# Goals

- 1. Primary goals
  2. Phase I: To determine the maximum tolerated dose of ibrutinib in combination with pembrolizumab in patients with advanced melanoma.
  3. Dose Expansion Cohort: To estimate the overall response rate treated at the maximum tolerated dose of ibrutinib in combination with pembrolizumab in patients with advanced melanoma.
  4. Secondary goals
  5. To assess the safety and adverse-event profiles of combination of ibrutinib with pembrolizumab in patients with advanced melanoma.
  6. To evaluate the overall response rate (ORR) in patients with advanced melanoma receiving ibrutinib and pembrolizumab.
  7. To evaluate the duration of response, progression-free survival (PFS), and overall survival (OS) in patients with advanced melanoma receiving ibrutinib and pembrolizumab.
  8. To assess the effect of treatment with ibrutinib and pembrolizumab on Th1/Th2 immune polarity.
  9. Exploratory goals
  10. To assess the CD8 T cell response to multiple melanoma-associated antigens, and to correlate CD8 T cell responses with changes in Th1/Th2 immune polarity
  11. To assess changes in plasma cytokines induced by treatment with ibrutinib and pembrolizumab
  12. To assess the change in potential biomarkers, such as tumor-bound and soluble PD-L1 levels and tumor-infiltrating lymphocytes, that may correlate with treatment responses.

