# Dosage Modification Based on Adverse Events

Strictly follow the modifications in this table for the first cycle, until individual treatment tolerance can be ascertained. Thereafter, these modifications should be regarded as guidelines to produce mild-to-moderate, but not debilitating, side effects. If multiple adverse events are seen, administer dose based on greatest reduction required for any single adverse event observed. Reductions or increases apply to treatment given in the preceding cycle and are based on adverse events observed since the prior dose.

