|  | Grade 2 | *Hold pembrolizumab until resolves to ≤Grade 1 Discontinue if does not resolve to ≤Grade 1 within 12 weeks after last dose administration | Hold until pembrolizumab is resumed  Resume at the next lower dose level (if occurs at 140 mg once daily, discontinue).  Discontinue if pembrolizumab  is discontinued, and enter Event Monitoring |

| **System/Organ/Class (SOC)** | **ADVERSE EVENTS/SYMPTOMS** | **ACTIONS** | |
| --- | --- | --- | --- |
|  |  | **Pembrolizumab** | **Ibrutinib** |
|  | Grade ≥3 | Hold pembrolizumab. If resolves to ≤Grade 1 within 72 hours resume treatment  If not, discontinue and enter Event Monitoring | Hold until pembrolizumab resumed  Resume at the next lower dose level (if occurs at 140 mg once daily, discontinue).  Discontinue if pembrolizumab is discontinued, and enter Event Monitoring |
| Other non-laboratory Adverse Events |  | | |
|  | Grade 3 | *Hold pembrolizumab until resolves to ≤Grade 1 Discontinue if does not resolve to ≤Grade 1 within 12 weeks after last dose administration | Hold until pembrolizumab resumed Resume at the next lower dose level (if occurs at 140 mg once daily, discontinue).  Discontinue if pembrolizumab is discontinued, and enter Event Monitoring |
|  | Grade 4 | Discontinue and enter Event Monitoring | Discontinue and enter Event Monitoring |

*If ibrutinib is discontinued according to Table 8.2, continue pembrolizumab until disease progression or intolerance develops or patient refusal.

- 1. Modifications Based on Concomitant Medications and Procedures for Ibrutinib
     - **Dose Modifications for Use with CYP3A Inhibitors and Inducers**

Ibrutinib is metabolized primarily by CYP3A. Avoid co-administration with strong CYP3A4 or moderate CYP3A inhibitors and consider alternative agents with less CYP3A inhibition.

- - - - If a strong CYP3A inhibitor (eg, ketoconazole, posaconazole, indinavir, nelfinavir, ritonavir, saquinavir, clarithromycin, telithromycin, itraconazole, nefazadone, or cobicistat) must be used, reduce ibrutinib to 140 mg for the duration of the inhibitor or withhold ibrutinib treatment temporarilty (for 7 days or less). Pembrolizumab may be continued at current dose. If unable to discontinue strong CYP3A inhibitor use within 12 weeks then permanently discontinue ibrutinib.

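### A DLT-free patient who received no pembrolizumab in Cycle 1 still counts as tolerating the combination

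*Protocol*

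**What the plan says.** The phase I goal in Section 2 is "To determine the maximum tolerated dose of ibrutinib in combination with pembrolizumab in patients with advanced melanoma". The treatment table in Section 7 starts ibrutinib on Day 1 and gives pembrolizumab as an "IV injection on Day 8 of Cycle 1", with "Cycle 1 treatment = 28 days".

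For most nonhematologic events a DLT is "≥Grade 3 per NCI Common Terminology Criteria for Adverse Events (CTCAE) version 4.0". Grade 3 rash or fever counts only if it occurs despite maximal support. Sections 7 and 16.2 set the MTD at no more than one DLT in six patients before Cycle 2. They apply the 3+3 steps to patients treated at the level and name no minimum exposure. The replacement rule reads "If a patient fails to complete the first cycle of treatment for reasons other than toxicity, an additional patient will be enrolled".

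On dose modification, Section 8 says: "Strictly follow the modifications in this table for the first cycle, until individual treatment tolerance can be ascertained". For events at least possibly related to study treatment, Table 8.2 holds pembrolizumab at Grade 2 for rash, diarrhea, hepatic dysfunction, pneumonitis, nephritis, hypophysitis and other immune-related events. For Grade 2 rash the ibrutinib instruction is "Hold until pembrolizumab is resumed", followed by a restart one level lower. Grade 2 myocarditis stops both drugs.

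Section 16.3 adds safety checks after 3 and 6 expansion patients have completed Cycle 1. One DLT in 3, or two in 6, lowers the starting dose. Section 16.6 treats every eligible, consented patient who began treatment as evaluable for safety.

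**The concern.** The question in phase I is whether ibrutinib at a given level is tolerable together with pembrolizumab. A patient whose Day 8 infusion is withheld through Day 28 gives no information on that, yet fills one of the three or six places as a success. Replacement does not remove this patient, because the reason was toxicity or because Cycle 1 is regarded as completed. The counting rule does not either, because it asks only for treatment at the level and absence of a DLT.

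The direction matters more than the loss of one observation. The patients affected are those who already had a toxicity, and each is scored in favour of the dose. The background section reports Grade 3 rash in both of the first two patients (at 560 mg) within a week of the first pembrolizumab dose. A patient who receives no pembrolizumab in the DLT window cannot show that signal there.

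Two decisions depend on the count: the declaration of Dose Level 1 as the MTD, and the choice at the expansion checks to keep or lower the starting dose.

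**Working it through.** **Plan's own figures.** The escalation size of 9 to 18 reproduces: 3 patients at the starting level plus 6 at Dose Level 1 gives 9, and 3 levels × 6 gives 18. The 11 enrolled are 5 at Dose Level 0 plus 6 at Dose Level 1. The protocol gives no operating characteristics for the 3+3 rule, so there is no probability to reproduce.

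**Window.** Combined treatment inside the DLT window lasts at most Day 8 to Day 28: 28 − 8 + 1 = 21 days. A hold that starts by Day 8 and lasts to Day 28 leaves none.

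**Tracing one patient.** Take a patient at Dose Level 1 with a treatment-related Grade 2 rash that begins in Days 1–7 and does not settle within Cycle 1.

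1. DLT? No: Grade 2 is below the threshold.
2. Day 8 pembrolizumab? Held under Table 8.2.
3. Replaced? No: either Cycle 1 was completed, or the reason for not completing it was toxicity.
4. Excluded from the 3 or 6? No rule in Section 7 or 16.2 does so.
5. Contribution to the MTD decision: one patient without a DLT.

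**Size, as an illustration.** The DLT rate p and the number k of the six without combined exposure are assumptions; neither is in the protocol. Give those k patients no DLT risk. The chance that the level passes is then

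P(≤1 DLT) = (1−p)^n + n·p·(1−p)^(n−1), with n = 6 − k.

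At p = 0.30:
- n = 6: 0.1176 + 0.3025 = 0.420
- n = 5: 0.1681 + 0.3602 = 0.528
- n = 4: 0.2401 + 0.4116 = 0.652

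| Assumed p | k = 0 | k = 1 | k = 2 |
| --- | --- | --- | --- |
| 0.30 | 0.420 | 0.528 | 0.652 |
| 0.40 | 0.233 | 0.337 | 0.475 |

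**Expansion checks.** Reading the checks as applying to the first 3 and 6 expansion patients, the dose is kept if there is no DLT in the first 3 and at most one in the next 3. At p = 0.30 this is 0.343 × 0.784 = 0.269. With one unexposed patient among the first 3 it is 0.7² × 0.784 = 0.384. With one among the next 3 it is 0.343 × (1 − 0.3²) = 0.312.

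**The case against.** **No sentence says how such a patient is scored.** True. The status follows from several rules read together. It follows by default, though: the steps need a count of patients treated and a count of DLTs, and this patient enters the first and not the second.

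**Table 8.2 is unclear before any pembrolizumab has been given.** The rash row speaks of resuming pembrolizumab and dates its 12-week limit from the last dose, and Section 8 ties reductions to treatment in the preceding cycle. This stands as a limit on any worked example, and a late infusion within Cycle 1 is conceivable. The Grade 2 myocarditis row does not depend on that wording, however: it stops both drugs, is below the DLT grade, and allows no replacement because the reason is toxicity.

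**Other safeguards exist.** The MTD definition runs to the start of Cycle 2, which a hold may delay, but a longer window without pembrolizumab adds no combined exposure. Section 16.71 monitors toxicity throughout treatment and for 30 days afterwards. It can close enrollment temporarily, but it does not change the DLT count. Many triggers for a hold are themselves DLTs, so the gap covers only milder events.

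**An unseen SAP may define evaluability.** Possibly, but the protocol itself fixes whom to replace, and that is an enrollment decision taken during the trial.

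**Stronger readings.** A reader might infer that several of the 6 patients at Dose Level 1 never received the combination. The protocol reports nothing about their exposure. A reader might also treat an observed 1 of 6 as 1 of 5 whenever a patient was held or reduced. That holds only with no combined exposure; a patient reduced late may have had most of the 21 days. Nor should every DLT-free patient with an ibrutinib reduction be dropped while all DLTs are kept. Assuming a true rate of 0.30 and 20% of patients DLT-free but reduced late, the observed rate would become 0.30/0.80 = 0.375, and P(≤1 of 6) would fall from 0.420 to 0.274, a bias the other way.

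**Conclusion.** The point holds in a limited form. Under the stated rules, a DLT-free patient who received no pembrolizumab in Cycle 1 is counted as tolerating the combination, in the 3+3 steps and in the MTD definition. The expansion checks have no condition that prevents the same. The direction is toward declaring the dose tolerable.

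The size is unknown. Escalation is complete, and nothing shows that any of the 6 patients at Dose Level 1 was affected. The increase from 0.42 to 0.53 or 0.65 assumes a true DLT rate of 0.30 and exactly one or two of six patients with no combined exposure and no DLT risk. What remains open is how the declared MTD is read, and how the expansion checks are counted.

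**What to change.** In Sections 7.5, 16.2 and 16.3:

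- Count every DLT, whatever the exposure.
- Do not count a DLT-free patient who received no pembrolizumab in Cycle 1 toward the 3 or 6.
- Keep in the denominator any DLT-free patient who received the combination but had ibrutinib held or reduced for toxicity, and report these patients separately.
- Run each expansion check once 3, and then 6, patients who received the combination or had a DLT have completed Cycle 1. Monitoring under 16.71 continues meanwhile.

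For the 6 patients already treated at Dose Level 1, report how many received pembrolizumab in Cycle 1, how many had ibrutinib held or reduced in that cycle, and the DLT rate among those exposed to the combination.

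The cost is a counting rule and a re-tabulation of existing dosing data. The downside is that a safety check may wait for one more patient who is already planned. The rule also does not guarantee an unbiased rate. If held patients are frailer (assume 20% held, with a DLT risk of 0.50 had they been exposed, and 0.30 overall), the rest have (0.30 − 0.20 × 0.50)/0.80 = 0.25 and P(≤1 of 6) is 0.534. That is why the exposure table is needed as well. No dose or treatment-modification rule changes.

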# Dosage Modification Based on Adverse Events

Strictly follow the modifications in this table for the first cycle, until individual treatment tolerance can be ascertained. Thereafter, these modifications should be regarded as guidelines to produce mild-to-moderate, but not debilitating, side effects. If multiple adverse events are seen, administer dose based on greatest reduction required for any single adverse event observed. Reductions or increases apply to treatment given in the preceding cycle and are based on adverse events observed since the prior dose.

***ALERT:* ADR reporting may be required for some adverse events (See Section 10)**

- 1. Dose Levels

(Based on Adverse Events in Table 8.2)

| **Dose Level** | **Ibrutinib** | **Pembrolizumab** |
| --- | --- | --- |
| 1* | 420 mg PO once daily | 200 mg IV |
| -1 | 280 mg PO once daily | NA |
| -2 | 140 mg PO once daily | NA |

*Dose level 1 refers to the starting dose.

- 1. Dose Modifications Based on Adverse Events

NOTE: These modifications only apply if the adverse event is **possibly**, **probably**, or

**definitely** related to study treatment

| **System/Organ/Class (SOC)** | **ADVERSE EVENTS/SYMPTOMS** | **ACTIONS** | |
| --- | --- | --- | --- |
|  |  | **Pembrolizumab** | **Ibrutinib** |
| Blood and lymphatic | **Anemia** | | |
| system disorders | Grade 4 | Hold pembrolizumab until  ≤Grade 2 and etiology is  determined  If anemia is immune-mediated (at least possibly related to pembrolizumab), discontinue pembrolizumab | Discontinue ibrutinib |
|  | **Febrile neutropenia (See also Investigations/Neutrophil count decreased)** | | |
|  | Grade 3 | Hold until symptoms resolve to  ≤Grade 1 | Hold until symptoms resolve to  ≤Grade 1;  Resume at the next lower dose level (if occurs at 140 mg once daily, discontinue) |
|  | Grade 4 | Hold until symptoms resolve to  ≤Grade 1 | Discontinue ibrutinib |
| Cardiac disorders | **Cardiac arrythmias** | | |
|  | Grade 3 | Continue pembrolizumab | Hold until symptoms resolve to  ≤Grade 1, then resume Resume at the next lower dose level  (if occurs at 280 mg once daily or lower, discontinue ibrutinib) |
|  | Grade 4 | Discontinue and enter Event Monitoring. | Discontinue and enter Event Monitoring |

| **System/Organ/Class (SOC)** | **ADVERSE EVENTS/SYMPTOMS** | **ACTIONS** | |
| --- | --- | --- | --- |
|  |  | **Pembrolizumab** | **Ibrutinib** |
| Cardiac disorders | **Cardiac failure** (not due to immune-related myocarditis) | | |
|  | Grade 2 | Hold until symptoms resolve to  ≤Grade 1, then resume | Hold until symptoms resolve to  ≤Grade 1;  Resume at the next lower dose level (if occurs at 140 mg once  daily, discontinue) |
|  | Grade 3 or 4 | Discontinue and enter Event Monitoring. | Discontinue and enter Event Monitoring. |
| Cardiac disorders | **Myocarditis** | | |
|  | Grade 2+ | Discontinue and enter Event Monitoring. | Discontinue and enter Event Monitoring. |
| Endocrine Disorders | **Symptomatic Hypophysitis** | | |
|  | Grade 2 and 3 | Hold until symptoms resolved to ≤Grade 1, initiate systemic steroid (see Section 9.6) and physiologic replacement dose. Discontinue if does not resolve to ≤Grade 1 within 12 weeks after last dose of  pembrolizumab, and then enter Event Monitoring | Hold until pembrolizumab resumed. Resume at the next lower dose level (if occurs at 140 mg once daily, discontinue).  Discontinue if pembrolizumab is discontinued, and enter Event Monitoring. |
|  | Grade 4 | Discontinue and enter Event Monitoring. Initiate systemic steroid (see Section 9.6) and physiologic replacement dose | Discontinue and enter Event Monitoring. |
|  | **Hypothyroidism** | | |
|  |  | Isolated hypothyroidism may be managed with replacement therapy without treatment  interruption and without corticosteroids | Continue. |
|  | **Hyperthyroidism** | | |
|  | Grade 3 | Hold until symptoms resolved to ≤Grade 1, initiate systemic steroid (see Section 9.6) Discontinue if does not resolve to ≤ Grade 1 within 12 weeks after last dose administration, and enter Event Monitoring | Hold until pembrolizumab resumed  Resume at the next lower dose level (if occurs at 140 mg once daily, discontinue).  Discontinue if pembrolizumab is discontinued, and enter Event Monitoring |
|  | Grade 4 | Discontinue and enter Event Monitoring. Initiate systemic steroid treatment | Discontinue and enter Event Monitoring |
| Gastrointestinal Disorders | **Diarrhea** | | |
|  | Grade 2 with symptoms  <1 week | *Hold until symptoms resolved to ≤Grade 1. Discontinue if does not resolve to ≤Grade 1 within 12 weeks after last dose of pembrolizumab, and then enter Event Monitoring | Hold until pembrolizumab resumed  Resume at the next lower dose level (if occurs at 140 mg once daily, discontinue).  Discontinue if pembrolizumab  is discontinued, and enter Event Monitoring |

| **System/Organ/Class (SOC)** | **ADVERSE EVENTS/SYMPTOMS** | **ACTIONS** | |
| --- | --- | --- | --- |
|  |  | **Pembrolizumab** | **Ibrutinib** |
|  | Grade 2 with symptoms  >1 week or Grade 3 | *Hold until symptoms resolved to ≤Grade 1, initiate systemic steroid (see Section 9.6) Discontinue if does not resolve to ≤Grade 1 within 12 weeks after last dose administration, and enter Event Monitoring | Hold until pembrolizumab resumed  Resume at the next lower dose level (if occurs at 140 mg once daily, discontinue).  Discontinue if pembrolizumab is discontinued, and enter Event Monitoring |
|  | Grade 4 | Discontinue and enter Event Monitoring  Initiate systemic steroid treatment (see Section 9.6) | Discontinue and enter Event Monitoring |
|  | **Nausea and Vomiting** | | |
|  | Grade ≥3 despite optimal  anti-emetic therapy | Continue if Grade 3  Hold if >Grade 3 until resolves  to ≤Grade 1 | Hold  Resume according to Table 8.2 |
| Investigations | Hepatic Dysfunction (**AST** or **ALT** or total **bilirubin**) and immune-mediated hepatitis | | |
|  | Grade 2  (AST or ALT >3 × and  <5 × ULN  or total bilirubin >1.5 × and <3 × ULN) | *Hold until levels resolve to  ≤Grade 1  (AST or ALT ≤3× ULN,  total bilirubin ≤1.5 × ULN)  Consider initiating systemic steroid treatment (see Section 9.6)  Discontinue if does not resolve to ≤Grade 1 within 12 weeks after last dose administration,  and enter Event Monitoring | Hold until pembrolizumab resumed  Resume at the next lower dose level (if occurs at 140 mg once daily, discontinue).  Discontinue if pembrolizumab is discontinued, and enter Event Monitoring |
|  | Grade 3  (AST or ALT >5 × ULN or  total bilirubin >3 ×ULN) or for patients with liver metastasis who begin treatment with Grade 2 AST or ALT, if AST or ALT increases by greater than or equal to 50%  relative to baseline and lasts ≥1 week | Discontinue and enter Event Monitoring  Initiate systemic steroid treatment (see Section 9.6) | Discontinue and enter Event Monitoring. |
| Immune System Disorders | **Immune-related Adverse Events** | | |
|  | Grade 2 | *Hold until symptoms resolved to ≤Grade 1, initiate systemic steroid (see 9.6). Discontinue if does not resolve to ≤Grade 1 within 12 weeks after last dose administration, and enter Event Monitoring. | Hold until pembrolizumab resumed. Resume at the next lower dose level (if occurs at 140 mg once daily, discontinue).  Discontinue if pembrolizumab is discontinued, and enter Event Monitoring |
|  | Grade ≥3 (except gastrointestinal and endocrine disorders) | Discontinue and enter Event Monitoring  Initiate systemic steroid treatment | Discontinue and enter Event Monitoring |

| **System/Organ/Class (SOC)** | **ADVERSE EVENTS/SYMPTOMS** | **ACTIONS** | |
| --- | --- | --- | --- |
|  |  | **Pembrolizumab** | **Ibrutinib** |
| Infections and | **Infectious Disorders** | | |
| infestations | Grade ≥3 | *Hold  If ibrutinib is held resume if  ≤Grade 1 or baseline | Hold until ≤Grade 1 or  baseline  Resume at the next lower dose level (if occurs at 140 mg once  daily, discontinue). |
| Injury, poisoning and | **Infusion-related Reaction** | | |
| procedural complications | Grade ≥3 | Discontinue and enter Event Monitoring | Discontinue and enter Event Monitoring |
| Investigations | **Neutrophil count decreased (See also Blood and lymphatic systems disorders/Febrile neutropenia)** | | |
|  | Grade ≥3 neutropenia with  infection or  Grade 4 neutropenia | *Hold until ≤Grade 2 Discontinue if does not resolve to ≤Grade 2 within 12 weeks  after last dose administration, and enter Event Monitoring. | Hold until ≤Grade 1 or baseline  Resume at the next lower dose level (if occurs at 140 mg once  daily, discontinue). |
|  | **Platelet count decreased** | | |
|  | Platelet counts <25 x 10^9^/L or platelet counts <50 x 10^9^/L with clinically significant bleeding events | *Hold until ≤Grade 2 Discontinue if does not resolve to ≤Grade 2 within 12 weeks  after last dose administration, and enter Event Monitoring | Hold until ≤Grade 1 or baseline  Resume at the next lower dose  level (if occurs at 140 mg once daily, discontinue). |
| Renal and urinary disorders | **Acute kidney injury** | | |
|  | Nephritis Grade 2 | *Hold until symptoms resolved to ≤Grade 1, initiate systemic steroids (see 9.6). Discontinue if does not resolve to ≤Grade 1 within 12 weeks after last dose administration, and enter Event Monitoring | Hold until pembrolizumab is resumed  Resume at the next lower dose level (if occurs at 140 mg once daily, discontinue).  Discontinue if pembrolizumab is discontinued, and enter  Event Monitoring |
|  | Grade ≥3 | Discontinue and enter Event Monitoring | Discontinue and enter Event Monitoring |
| Respiratory, thoracic, and mediastinal disorders | **Pneumonitis** | | |
|  | Grade 2 | *Hold until symptoms resolved to ≤Grade 1, initiate systemic steroids  Discontinue if does not resolve to ≤Grade 1 within 12 weeks after last dose administration, and enter Event Monitoring | Hold until pembrolizumab resumed  Resume at the next lower dose level (if occurs at 140 mg once daily, discontinue).  Discontinue if pembrolizumab is discontinued, and enter Event Monitoring |
|  | Grade ≥3 | Discontinue and enter Event Monitoring | Discontinue and enter Event Monitoring |
| Skin and subcutaneous tissue disorders | **Rash maculo-papular** | | |
|  | Grade 2 | *Hold pembrolizumab until resolves to ≤Grade 1 Discontinue if does not resolve to ≤Grade 1 within 12 weeks after last dose administration | Hold until pembrolizumab is resumed  Resume at the next lower dose level (if occurs at 140 mg once daily, discontinue).  Discontinue if pembrolizumab  is discontinued, and enter Event Monitoring |

| **System/Organ/Class (SOC)** | **ADVERSE EVENTS/SYMPTOMS** | **ACTIONS** | |
| --- | --- | --- | --- |
|  |  | **Pembrolizumab** | **Ibrutinib** |
|  | Grade ≥3 | Hold pembrolizumab. If resolves to ≤Grade 1 within 72 hours resume treatment  If not, discontinue and enter Event Monitoring | Hold until pembrolizumab resumed  Resume at the next lower dose level (if occurs at 140 mg once daily, discontinue).  Discontinue if pembrolizumab is discontinued, and enter Event Monitoring |
| Other non-laboratory Adverse Events |  | | |
|  | Grade 3 | *Hold pembrolizumab until resolves to ≤Grade 1 Discontinue if does not resolve to ≤Grade 1 within 12 weeks after last dose administration | Hold until pembrolizumab resumed Resume at the next lower dose level (if occurs at 140 mg once daily, discontinue).  Discontinue if pembrolizumab is discontinued, and enter Event Monitoring |
|  | Grade 4 | Discontinue and enter Event Monitoring | Discontinue and enter Event Monitoring |

*If ibrutinib is discontinued according to Table 8.2, continue pembrolizumab until disease progression or intolerance develops or patient refusal.

- 1. Modifications Based on Concomitant Medications and Procedures for Ibrutinib
     - **Dose Modifications for Use with CYP3A Inhibitors and Inducers**

Ibrutinib is metabolized primarily by CYP3A. Avoid co-administration with strong CYP3A4 or moderate CYP3A inhibitors and consider alternative agents with less CYP3A inhibition.

- - - - If a strong CYP3A inhibitor (eg, ketoconazole, posaconazole, indinavir, nelfinavir, ritonavir, saquinavir, clarithromycin, telithromycin, itraconazole, nefazadone, or cobicistat) must be used, reduce ibrutinib to 140 mg for the duration of the inhibitor or withhold ibrutinib treatment temporarilty (for 7 days or less). Pembrolizumab may be continued at current dose. If unable to discontinue strong CYP3A inhibitor use within 12 weeks then permanently discontinue ibrutinib.
      - If a moderate CYP3A inhibitor (eg, erythromycin, amprenavir, aprepitant, atazanavir, ciprofloxacin, crizotinib, diltiazem, fluconazole, voriconazole, fosamprenavir, imatinib, verapamil, amiodarone, or dronedarone) must be used, reduce ibrutinib to 280 mg once daily for the duration of the inhibitor use. Avoid grapefruit and Seville oranges during ibrutinib treatment, as these are moderate inhibitors of CYP3A. (See Appendix V.)
      - No dose adjustment is required in combination with mild inhibitors.

Avoid concomitant use of system strong CYP3A inducers (e.g. carbamazepine, rifampin, phenytoin and St. John’s wort) should be avoided. Consider alternative medications with less CYP3A induction.

A list of common CYP3A inhibitors and inducers is provided in Appendix V. A comprehensive list of inhibitors, inducers, and substrates may be found at [http://medicine.iupui.edu/clinpharm/ddis/main-table/.](http://medicine.iupui.edu/clinpharm/ddis/main-table/) This website is continually revised and should be checked frequently for updates.

For the most comprehensive effect of CYP3A inhibitors or inducers on ibrutinib exposure, please refer to the current version of the IB.

- - - Concurrent use with QT Prolongation Agents

Ibrutinib is not known to prolong the QT interval, but it may affect the pharmacokinetics of other medications. Any medications known to cause QT prolongation should be used with caution; periodic ECG and electrolyte monitoring should be considered.

- - - **Dose modification for bleeding-related events (Antiplatelet Agents and Anticoagulants)**

Use ibrutinib with caution in subjects requiring anticoagulants or medications that inhibit platelet function. In an in vitro platelet function study, inhibitory effects of ibrutinib on collagen-induced platelet aggregation were observed. Supplements such as fish oil and vitamin E preparations should be avoided during treatment with ibrutinib. Bleeding events of any grade, including bruising and petechiae, occurred in subjects treated with ibrutinib. Ibrutinib should be held at least ~~3 to~~ 7 days pre- and post-surgery depending upon the type of surgery and the risk of bleeding (see section

on Dose modification for invasive procedures or surgery). Subjects with congenital bleeding diathesis have not been studied.

Subjects requiring the initiation of therapeutic anticoagulation therapy (eg, atrial fibrillation) should be monitored closely for signs and symptoms of bleeding and the risks and benefits of continuing ibrutinib treatment should be considered.

- - - **Dose modification for invasive procedures or surgery**

Ibrutinib may increase risk of bleeding with invasive procedures or surgery. The following guidance should be applied to the use of ibrutinib in the perioperative period for subjects who require surgical intervention or an invasive procedure while receiving ibrutinib:

- - - - For minor procedures (such as a central line placement, skin or needle biopsy, lumbar puncture [other than shunt reservoir access], thoracentesis, or paracentesis) ibrutinib should be held for at least 3 days prior to the procedure and should not be restarted at least 3 days after the procedure. For bone marrow biopsies, that are performed while the subject is on ibrutinib, it is not necessary to hold ibrutinib.
      - For any surgery or invasive procedure requiring sutures or staples for closure, ibrutinib should be held at least 7 days prior to the intervention (except for emergency procedures) and should be held at least 7 days after the procedure and restarted at the discretion of the investigator when the surgical site is reasonably healed without serosanguineous drainage or the need for drainage tubes.
    - **Dose modification for liver impairment subjects**

Ibrutinib is metabolized in the liver and therefore subjects with clinically significant hepatic impairment (Child- Pugh class B or C) are excluded from study participation in our initial phase 2 study, and lower starting dose was given in subjects with Child - Pugh Class A liver impairment (280 mg daily).

In this modified phase 1 study, patients with clinical evidence of liver impairement (Child – Pugh Class A, B, and C) at the time of screening are already excluded from particitipating, in addition to a lowered starting dose at 420 mg daily (compared to 520 mg in the initial study), to reduce any significant adverse effects. Therefore, for any liver impairment during the course of the treatment, the dose modification will follow the guideline in table 8.1 and 8.2, and no further modifications will be needed. It is critical for providers to monitor subjects for signs of toxicity and follow dose modification guidance as needed (Refer to Appendix 4 Table 8.1).

